The association between ASD and BD in adult subjects has been repeatedly confirmed, and lithium has been suggested as the first treatment option for high-functioning ASD with comorbid BD [33]. Similarly, children and adolescents with ASD have high rates of comorbid BD, up to 4–7% in clinical cohorts [34,35], and often experience irritability, aggression, self-injury, and tantrums, as well as subclinical manic symptoms including elation, expansive mood, and racing thoughts [32]. Also, it is increasingly recognized that comorbid BD significantly contributes to the morbidity associated with ASD [36], although the communication difficulties and the frequently low intellectual functioning complicate the identification of comorbid clinical pictures in this population [37]. To further increase this clinical complexity, BD in ASD is often characterized by atypical features, such as irritability and behavioral disturbances, which are frequently associated with several other potentially comorbid conditions, including, above all, ADHD [37,38]. Finally, suicidal behaviors are also frequently observed in ASD-BD patients and may confer a greater risk of hospitalization [39,40] since ASD is an independent risk factor for suicide, with a probability to die by suicide which is ten times greater than in the general population [41].

Despite these considerations, research so far has only scarcely targeted this comorbid population to define guidelines for the clinical management of associated morbidity. Pharmacological treatment options available for ASD with comorbid BD are not directed to the core symptoms of the disorder but rather target challenging behaviors associated with comorbidities [32]. Second-generation antipsychotics (SGAs)—i.e., Risperidone and Aripiprazole—are currently approved by FDA and EMA for treating irritability and aggression in ASD youths [42]. Approximately 65% of ASD-BD patients treated with SGAs showed an improvement greater than 30% in irritability, and despite an atypical severity of BD symptoms in ASD youths, the presence of this comorbidity does not impact the relative rate of response [43]. However, given the high risk of SGA-related side effects, including weight gain and metabolic disorders, increased serum prolactin, and sedation, antipsychotics should be used cautiously [32].

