### 2.2. Recruitment

Patients will be consecutively enrolled after assessment at our hospital for eligibility. Those who meet the eligibility criteria listed below will be included following a thorough clinical screening. All participants and their caregivers will be informed about the assessment procedure, and participation in the study will be voluntary. Recruited patients and their parents will be asked to provide their signed informed consent. Additionally, patients will be allowed to withdraw their consent any time during the study.

Inclusion criteria will be as follows: lithium-naïve adolescent inpatients or outpatients aged 12 to 18 years; informed consent obtained from the patient and both caregivers; diagnosis of Bipolar or Related Disorders (Bipolar Disorder type I (BD-I), Bipolar Disorder type II (BD-II), Cyclothymic Disorder, Other Specified or Unspecified Bipolar Disorder) with or without a diagnosis of Autism Spectrum Disorder according to the Diagnostic and Statistical Manual of Mental Disorders, Fifth Edition, Text Revision (DSM-5-TR); cognitive functioning within the borderline to normal range (i.e., Full-Scale Intelligence Quotient (FSIQ) or General Ability Index (GAI) ≥ 70); current presence of Self-Injurious Thoughts and/or Behaviors (SITB) (i.e., including non-suicidal self-injury (NSSI), intentional self-harm, suicide ideation, plans or preparations, or suicide attempts) as assessed through clinical interview (i.e., investigated by administering the Columbia—Suicide Severity Rating Scale); current presence of Emotional Dysregulation (ED) and/or irritability as assessed by means of standardized clinical measures (i.e., Reactivity, Intensity, Polarity, and Stability questionnaire for Youth and/or Affective Reactivity Index above the clinical cutoff). These latter criteria will be considered to ensure a relatively high clinical severity of the included sample.

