### 2.3. Procedure and Assessment

A matching number of BD patients with and without comorbid ASD will be recruited. The ASD-BD group will be the experimental arm of the study, with the BD-only group as the clinical comparator. Both groups will be followed up for six months after recruitment while receiving treatment with Extended-Release Lithium Salts for clinical indication. Primary and secondary outcome measures will be acquired before treatment initiation (T0), as well as three (T1) and six (T2) months after reaching stable drug dosage (Steady State—SS). At T0, patients will be screened for eligibility and carefully evaluated by means of the following diagnostic tools: the semi-structured DSM-5-based clinical interview Kiddie Schedule for Affective Disorders and Schizophrenia—Present and Lifetime version (K-SADS-PL); the Wechsler Intelligence Scale for Children—fourth edition (WISC-IV); the Autism Diagnostic Observation Schedule—second edition (ADOS-2); and the Autism Diagnostic Interview—Revised (ADI-R).

At each timepoint (T0, T1, and T2), patients will be thoroughly assessed as for clinical routine. The following rating scales will be filled in by clinicians based on parents’ and caregivers’ reports: the Clinical Global Impression (CGI) scale scores and the Children Global Assessment Scale (CGAS) scores. Patients will be also administered the following clinical interviews: the Children Depression Rating Scale (CDRS); the Young Mania Rating Scale (YMRS); the Columbia—Suicide Severity Rating Scale (C-SSRS); the Deliberate Self-Harm Inventory (DSHI); Reactivity, Intensity, Polarity and Stability questionnaire for Youth (RIPoSt-Y). Caregivers will be administered the following clinical rating scales: the Modified Overt Aggression Scale (MOAS) and the Affective Reactivity Index (ARI).

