### 2.6. Statistical Analyses

Statistical analysis will be performed using RStudio^®^ (version 1.3.1093, RStudio, PBC, Boston, MA, USA). Non-parametric tests for repeated measures (e.g., Wilcoxon signed rank test) will be used to analyze the psychiatric assessment score variations of the clinical rating scales described above. Additionally, multiple linear regression models will be performed to detect the effect of the ASD diagnosis on the variations on patients’ clinical scores. Patients’ age and gender, ongoing treatment with other psychotropic drugs, and lithium plasma levels will be considered as covariates in multivariate analyses to account for possible specific effects.

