## 3. Discussion

The present study seeks to address a significant gap in the literature regarding the efficacy and tolerability of Extended-Release Lithium Salts in adolescents with Bipolar Disorder and comorbid Autism Spectrum Disorder. Lithium, widely recognized for its effectiveness in treating BD in the neurotypical population [1,2], has been insufficiently studied in individuals with ASD, particularly in youth populations [32,48,49]. The inclusion of Extended-Release Lithium Salts as a treatment modality in this population is a critical step toward understanding its potential benefits and limitations in this specific comorbid condition.

The longitudinal prospective design of the present study allows for a comprehensive assessment of both efficacy and safety, providing valuable insights into the clinical management of BD in ASD. By focusing on key outcome measures such as mood instability, suicidality, irritability, and aggression, which are prevalent in this population [32,41], the study aligns with the clinical challenges often observed in ASD-BD patients. The inclusion of a well-matched control group of neurotypical BD patients, in which lithium efficacy has been already established [1,2], further strengthens the study capacity to discern the specific effects of Extended-Release Lithium Salts in the context of comorbid ASD.

Another strength of the study is its naturalistic approach, which reflects real-world clinical settings and may enhance the generalizability of the findings. Additionally, the thorough assessment procedures, including the use of validated diagnostic tools and clinical rating scales, ensure a robust evaluation of both primary and secondary outcomes. The careful consideration of covariates, such as age, gender, and concurrent psychotropic treatments in the statistical analysis, will allow for a more nuanced understanding of the factors influencing treatment outcomes. Finally, the sample size calculated to achieve sufficient power will provide further statistical robustness.

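### The regression of score change on ASD diagnosis omits the T0 score of the same scale, and the control group is called well matched although only equal numbers are planned

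*Protocol article*

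**What the plan says.** All references are to the protocol article.

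- **Section 2.6, model.** The between-group analysis is described as follows: "multiple linear regression models will be performed to detect the effect of the ASD diagnosis on the variations on" patients' clinical scores. The outcome is change and the exposure is diagnosis.
- **Section 2.6, covariates.** Patients' "age and gender, ongoing treatment with other psychotropic drugs, and lithium plasma levels will be considered as covariates". No baseline score appears.
- **Section 2.3.** Every clinical scale is administered at T0, T1 and T2, so the baseline value of each outcome will be on file. On group formation the section says: "A matching number of BD patients with and without comorbid ASD will be recruited".
- **Section 2.2.** "Patients will be consecutively enrolled after assessment at our hospital for eligibility". No matching step or matching variable is described.
- **Section 3.** "The inclusion of a well-matched control group of neurotypical BD patients" is put forward as a strength that helps isolate effects specific to ASD. "The careful consideration of covariates, such as age, gender, and concurrent psychotropic treatments in the statistical analysis" is put forward as another. The limitations concede that the design is non-randomised, but link this to generalisability rather than to comparability of the groups.

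**The concern.** With non-randomised groups there is no reason to expect equal T0 scores. Change is correlated with the starting value: patients who start high tend to fall further whatever the treatment does. A change-score regression without the T0 score can therefore turn a baseline difference into an apparent ASD effect, in either direction. The aim is to show that the ASD group does no worse than the comparator, so such an artefact bears directly on the main conclusion.

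Selection adds to this. Section 2.2 requires RIPoSt-Y and/or ARI above the clinical cutoff at entry, and both are then re-scored as outcomes, so some regression to the mean on those scales is built in. Leaving out the T0 score also gives up precision in an analysis of about 40 patients.

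The matching claim matters because it tells readers that the comparability problem has been handled by design. Equal group sizes do not achieve that.

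**Working it through.** **1. Number analysed.** Section 2.5 gives effect size 1.06, error level 0.05, power 0.95, 20 per group, and 25 per group after 20% dropout. A one-sided two-sample t test with 20 per group has power 0.950, so the figure reproduces (two-sided, power would be 0.904; sidedness is a separate matter). Then 20 / (1 − 0.20) = 25. About 40 completers are expected, and nothing below changes that number.

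**2. Assumptions.** Let D be the T0 difference, ASD-BD minus BD-only, in baseline SDs, with higher meaning worse. Let r be the correlation between T0 and follow-up within groups. Baseline and follow-up SDs are taken as equal, so the slope is r. The documents give neither D nor r. The illustration uses D = 0.5 and r = 0.3, 0.5, 0.7.

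**3. Both groups regress to a common mean, no ASD effect given baseline.** Follow-up difference = rD. Change contrast = rD − D = −(1−r)D. The model with T0 is unbiased.

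**4. Each group is stable around its own mean.** Follow-up difference = D, so the change contrast is 0 and unbiased. The model with T0 predicts a follow-up difference of rD and assigns the remaining D − rD = (1−r)D to ASD. It is now the biased one, by the same amount with the opposite sign.

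**5. Between these cases.** Suppose the long-run means differ by kD, with k between 0 and 1. The change contrast is −(1−r)(1−k)D and the adjusted contrast is (1−r)kD. Their gap is (1−r)D whatever k is. Reporting both models therefore shows how much the answer depends on this choice.

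**6. Precision.** Change-score variance is 2(1−r); residual variance given T0 is 1−r²; the ratio is (1+r)/2. A baseline difference makes group and T0 score collinear, which multiplies the variance of the adjusted contrast by 1 + D²/4 = 1 + 0.25/4 = 1.0625 for equal groups.

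| r | (1−r) × 0.5 | False-positive rate, change without T0 | Same, with T0 | (1+r)/2 | × 1.0625 |
|---|---|---|---|---|---|
| 0.3 | 0.35 SD | 14.4% | 5.4% | 0.65 | 0.69 |
| 0.5 | 0.25 SD | 11.7% | 5.4% | 0.75 | 0.80 |
| 0.7 | 0.15 SD | 9.4% | 5.4% | 0.85 | 0.90 |

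The false-positive rates come from a simulation of scenario 3 only (4000 runs, 20 per group, two-sided 5%). That scenario favours the adjusted model by construction. With D = 0 both models stay near 5%.

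**7. Matching.** Section 2.3 promises equal numbers, section 2.2 promises consecutive enrolment, and no variable is named on which patients are matched. Section 3 claims good matching. The first two do not support the third.

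**The case against.** **Neither model is right by default.** This is the strongest objection, and it stands. Groups formed by diagnosis may well have different stable means, and then the change score is the unbiased analysis (step 4). The case for adding T0 is therefore a case for showing both models. It does not establish that the planned estimate is wrong.

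**A journal article condenses its protocol.** The Discussion introduces covariates with a such-as phrase, and a fuller plan may include T0. That is fair, but section 2.6 gives its list without any such qualifier, and the Discussion claims the covariates as a strength. If a fuller plan does adjust for T0, the article should say so.

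**Entry criteria set a common floor.** Both groups must have self-injurious thoughts or behaviours and emotional dysregulation or irritability. This narrows differences on some scales, but it sets no floor for YMRS, the scale used for the sample size, and does not equalise group means.

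**Readings that go too far.**

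- A reader might infer that the protocol identifies confounders and then ignores them. It calls nothing a confounder. The remark that atypical features of BD in ASD, "which are frequently associated with several other potentially comorbid conditions, including, above all, ADHD", concerns overlap that complicates diagnosis; it does not say that ADHD is commoner in one study group. The Introduction's statement on lithium, risperidone and ADHD concerns prepubertal youths and compares two drugs. It does not show that ADHD alters lithium response at ages 12 to 18.
- A reader might infer that the omission tilts the result toward non-inferiority. That needs the ASD group to start more severe. The phrase "despite an atypical severity of BD symptoms in ASD youths" gives no direction, and the same sentence goes on to say that the comorbidity does not affect the relative rate of response to second-generation antipsychotics.
- Omitting ADHD and BD subtype is a debatable covariate choice with about 40 completers, not an error.

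**Conclusion.** The point holds in two parts.

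First, the covariate list omits the T0 score of the outcome, which is collected and is the obvious candidate when change is compared between non-randomised groups. The choice can move the ASD contrast by (1−r) times the baseline difference. At r = 0.5, where the SD of change equals the baseline SD because √(2 × 0.5) = 1, the illustrative 0.25 SD is about 24% of the planning effect (0.25 / 1.06), if 1.06 is in SDs of change. All of these sizes rest on an assumed 0.5 SD imbalance, an assumed r and equal SDs. They show sensitivity to the choice of model. They do not show a known bias, and the sign cannot be determined from the documents. The precision gain also assumes equal SDs, and is modest: residual variance falls to 65–85% of the change-score variance, slightly less favourable for the group contrast if the groups differ at T0.

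Second, the good-matching claim in the Discussion contradicts the Methods. This part depends on no assumption.

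Both are worth correcting. Neither invalidates the design or alters the sample size.

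**What to change.** 1. In section 2.6, add the T0 score of the same scale as a pre-specified covariate in each regression of score change on ASD diagnosis. Report the model without it alongside as a sensitivity analysis, and say that the two rest on different assumptions about how the groups would evolve.
2. Optionally, examine ADHD (from the T0 K-SADS-PL) and BD subtype as further sensitivity covariates. With about 40 completers they need not enter the main model. Whether lithium plasma level belongs in the list is a separate question, and this change does not depend on it.
3. In section 3, replace the phrase describing the controls with *equal-sized group of BD patients without ASD*. This also avoids the word neurotypical, which the article uses as shorthand for the absence of ASD although the criteria in section 2.2 do not exclude ADHD.

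Cost: wording only, no new data and no change in sample size. The small downside is one more model term and two sets of estimates that may disagree; any disagreement should be reported.

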## 3. Discussion

The present study seeks to address a significant gap in the literature regarding the efficacy and tolerability of Extended-Release Lithium Salts in adolescents with Bipolar Disorder and comorbid Autism Spectrum Disorder. Lithium, widely recognized for its effectiveness in treating BD in the neurotypical population [1,2], has been insufficiently studied in individuals with ASD, particularly in youth populations [32,48,49]. The inclusion of Extended-Release Lithium Salts as a treatment modality in this population is a critical step toward understanding its potential benefits and limitations in this specific comorbid condition.

The longitudinal prospective design of the present study allows for a comprehensive assessment of both efficacy and safety, providing valuable insights into the clinical management of BD in ASD. By focusing on key outcome measures such as mood instability, suicidality, irritability, and aggression, which are prevalent in this population [32,41], the study aligns with the clinical challenges often observed in ASD-BD patients. The inclusion of a well-matched control group of neurotypical BD patients, in which lithium efficacy has been already established [1,2], further strengthens the study capacity to discern the specific effects of Extended-Release Lithium Salts in the context of comorbid ASD.

Another strength of the study is its naturalistic approach, which reflects real-world clinical settings and may enhance the generalizability of the findings. Additionally, the thorough assessment procedures, including the use of validated diagnostic tools and clinical rating scales, ensure a robust evaluation of both primary and secondary outcomes. The careful consideration of covariates, such as age, gender, and concurrent psychotropic treatments in the statistical analysis, will allow for a more nuanced understanding of the factors influencing treatment outcomes. Finally, the sample size calculated to achieve sufficient power will provide further statistical robustness.

Limitations of the study could include the non-randomized design and the lack of a control mediation (e.g., other mood stabilizers), as well as the comparison between different lithium formulation (e.g., extended versus immediate-release lithium formulation). These factors limit the generalizability of the results and underscore the need for further randomized controlled trials to confirm our future findings. Nonetheless, the longitudinal prospective naturalistic design of our intervention study will have significant benefits, including those related to its real-world setting, which provides insights into how interventions work in everyday life, enhancing the external validity of the findings.

## 4. Conclusions

This study will have the potential to make a significant contribution to the field. By investigating the efficacy and safety of Extended-Release Lithium Salts in a previously under-investigated population, it may provide critical evidence to guide clinical practice and inform future research. The study findings could pave the way for more personalized treatment approaches for adolescents with BD and comorbid ASD, ultimately improving outcomes for this vulnerable population. Specifically, if the results show that lithium offers advantages over harmful BD-related outcomes in youth with ASD, such as suicidality, while maintaining a manageable side effect profile, our study will assist clinicians in considering this often overlooked treatment option for this highly vulnerable group.

## Data Availability

No new data were created.
